#### Quality of life (QoL)

QoL is assessed with the validated 30-item self-assessment questionnaire of the European Organisation for Research and Treatment of Cancer (EORTC QLQ-C30, version 3.0). It includes five multi-item functional scales (physical, role, emotional, cognitive, and social function), three multi-item symptom scales (fatigue, pain, nausea/vomiting) and six single items assessing further symptoms (dyspnea, insomnia, appetite loss, constipation, diarrhea) and financial difficulties [51]. In addition, the 29-item high-dose chemotherapy (EORTC QLQ-HDC-29) is applied, assessing common problems after stem cell transplantation, e.g. gastro-intestinal side-effects and worry/anxiety [52]. Scores will be derived according to the EORTC scoring manual. Reference values are available from the EORTC reference manual, a review, including 2,800 patients before and after HCT [53] and from a sample of the general German population stratified by gender and age [54]. Furthermore, evidence-based guidelines for the interpretation of the clinical relevance of changes in the different EORTC QLQ-C30 subscales were recently published [55], categorizing differences between scores in trivial, small, medium or large effect sizes.

#### Fatigue

Fatigue will be assessed with the Multidimensional Fatigue Inventory (MFI) which is a 20-item, multidimensional self-assessment questionnaire that has been validated for a German-speaking population [56]. It covers five different dimensions of fatigue (general fatigue, physical fatigue, reduced activity, reduced motivation and mental fatigue). Scores are derived by summing the answers (five-stage scale) of the appropriate items. Reference values of the MFI scores are available from a representative sample of the German population including 2,037 subjects [57]. The use of the MFI is recommended in cancer patients [58].

#### Distress

Distress will be assessed with the Distress-Thermometer, developed from the National Comprehensive Cancer Network (NCCN) as a screening tool [59, 60]. The Distress-Thermometer has already been validated in stem cell transplantation patients [61].

#### Depression

Depressive symptoms are assessed with the 20-item Center for Epidemiological Studies Depression Scale (CES-D). The CES-D scale is a widely used validated self-report instrument to measure current depressive symptomatology and to identify possible cases of depressive disorders, both in the general population and in patients with cancer [62].

#### Locus of control

Locus of control is measured by a validated German 21-item questionnaire *Assessment of health and sickness locus of control* (KKG). It comprises 3 subscales, assessing internal, social external and fatalistic external locus of control [63]. The questionnaire is based on the Multidimensional Health Locus of Control Scale (MHLC) [64].

#### Cognitive function

The cognitive function (concentration, cognitive flexibility) is estimated using the trail-making-test. This is a standardized, reliable and valid measure used in neuropsychological diagnostics [65, 66]. The test measures the time needed by the participant to connect numbers and letters spread over a sheet of paper in a logical sequence.

#### Biomarkers

Serum and PBMCs are derived from whole peripheral blood samples, processed within 4 h after taking the blood sample and stored at −80 °C or cryopreserved in liquid nitrogen (PBMCs) for analyses of biomarkers. Urine samples are collected for analyses of biomarkers of oxidative stress, i.e. urinary F2-isoprostane and 8-oxo-dG measured by chromatography-based methodology. Blood samples are collected for analyses of biomarkers of GvHD, i.e. inflammatory (e.g. IL-1, IL-4, IL-10, TNF-α) and endothelial parameters (e.g. angiopoetin-2, thrombomodulin (sTM)) measured by ELISA.

#### Side-effects of cancer treatment

Severity and duration of GvHD will be recorded by attending physicians every week according to the classification by Thomas et al. [67]. Furthermore, during allo-HCT and up to day 100 after, common side effects like nausea, diarrhea, appetite loss, pain, fatigue, concentration difficulties and anxiety are assessed weekly during phone calls using a visual analogue scale. After day 100 until the end of intervention (day 365 after) patients are questioned on these parameters during every phone call (depending on clinical status every 2–4 weeks). Infections are documented via medical chart review.

#### Safety issues

Potential adverse events (AEs) and serious adverse events (SAEs) causally related to the intervention or assessment procedure will be recorded. Patients are informed about contraindications for exercise sessions (thrombopenia, bleeding, infections including fever, dizziness, strong nausea/ vomiting, and strong pain) and advised to stop exercising when they feel that symptoms get stronger.

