**Methods/design:**

The PETRA study is a randomized, controlled intervention trial investigating the effects of a yearlong partly supervised mixed exercise intervention (endurance and resistance exercises, 3–5 times per week) in 256 patients during and after allogeneic stem cell transplantation. Patients in the control group perform progressive muscle relaxation training (Jacobsen method) with the same frequency. Main inclusion criterion is planned allo-HCT. Main exclusion criteria are increased fracture risk, no walking capability or severe cardiorespiratory problems. Primary endpoint is overall survival after two years; secondary endpoints are non-relapse mortality, median survival, patient reported outcomes including cancer related fatigue and quality of life, physical performance, body composition, haematological/immunological reconstitution, inflammatory parameters, severity of complications and side-effects (e.g. GvHD and infections), and cognitive capacity.

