### Interventions

The training starts at the same day as the conditioning treatment. Both intervention programs are performed 3–5 times per week for 12 months. During the first phase (hospital stay for allo-HCT) participants perform the program 3 times under supervision and guidance of an experienced therapist, 2 times self-directed. During the second phase (after discharge), patients perform both interventions self-directed at home. Until assessment on day 100 weekly phone calls in both groups will allow for adaptation of the program and enhance motivation/ adherence, 3 training sessions per week are recommended. After day 100 assessment, phone calls will take place every 2–3 weeks.

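### Recording only adverse events judged related to the intervention leaves falls, fractures, bleeding and cardiac events at home without a fair between-arm comparison

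*Protocol article*

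**What the plan says.** The rule is in the Safety issues section of the protocol article: "Potential adverse events (AEs) and serious adverse events (SAEs) causally related to the intervention or assessment procedure will be recorded". The next sentence there says that "Patients are informed about contraindications for exercise sessions"; no parallel statement is made for relaxation. The section does not say who decides that an event is causally related, or whether that person knows the arm.

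The Interventions section says: "During the second phase (after discharge), patients perform both interventions self-directed at home". Contact is then by telephone: "Until assessment on day 100 weekly phone calls in both groups", and at longer intervals afterwards.

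Other harm data are collected without a causality condition. In the section on side-effects of cancer treatment:

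- GvHD: "Severity and duration of GvHD will be recorded by attending physicians every week".
- Common symptoms up to day 100: these "are assessed weekly during phone calls using a visual analogue scale", and then at every call until day 365.
- Infections: "Infections are documented via medical chart review".

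Table 1 adds overall survival and non-relapse mortality as ongoing assessments, and treatment complications at t1 (discharge). The abstract lists among the secondary endpoints "severity of complications and side-effects (e.g. GvHD and infections), and cognitive capacity".

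**The concern.** The rule makes a causal judgement the condition for entering the data, when relatedness could be one attribute of a recorded event. An analysis plan cannot recover events that were never written down.

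The judgement can differ by arm. Participants and therapists cannot be masked to exercise or relaxation. The relaxation method has no aerobic or strengthening component, so a fall, fracture or cardiac event is easier to link to exercise. The error can also run the other way. The Background section notes a raised risk of cardiovascular events and pulmonary complications after transplantation, so an event that exercise did cause can be attributed to the transplant and dropped.

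At stake is the comparison of exercise-specific harm. The article's own exclusion criteria and session warnings name the hazards: fracture risk, unstable bone lesions, severe cardiac disease, low platelets, bleeding, dizziness. The conclusion states the hope of refining exercise guidelines, for which a fair account of harm is needed.

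**Working it through.** **1. Which harms have a record that does not depend on attribution?**

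| Harm | Source in the article | Causality filter? |
|---|---|---|
| Death, non-relapse mortality | Outcome measures; Table 1, ongoing | No |
| GvHD severity and duration | Side-effects section, weekly | No |
| Infections | Side-effects section, chart review | No |
| Nausea, diarrhea, appetite loss, pain, fatigue, concentration, anxiety | Side-effects section, phone calls to day 365 | No |
| Complications of treatment | Table 1, t1 only | No |
| Falls, fractures, musculoskeletal injury, bleeding, non-fatal cardiac events after discharge | Safety issues section only | Yes |

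Only the last row depends on attribution.

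**2. How long is the exposed period?** The article gives no length of hospital stay. Its schedule puts discharge (t1) before day 100 (t2), so the home phase covers at least 365 − 100 = 265 of the 365 days after transplantation.

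**3. What does the filter do to the comparison?** Let p be the true event probability in an arm and s the probability that an event there is judged related and so recorded. Then:

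- Recorded rate in an arm = p × s.
- Recorded rate ratio = (p_E / p_C) × (s_E / s_C), with E for exercise and C for control.

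The recorded ratio equals the true ratio only if s_E = s_C. The article gives no information on either s, so the second factor cannot be removed afterwards.

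**4. Illustration.** The denominator is the planned arm of 128 (Sample size section). That figure reproduces: the hazard ratio is ln 0.66 / ln 0.49 = 0.582, Schoenfeld's formula gives 108 events, and 108 / 0.425 = 254 patients against 256 stated. The point does not depend on it.

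The event rate and attribution probabilities below are **assumptions**; the article gives none. With a true rate of 10% in both arms, 0.10 × 128 = 12.8, about 13 events per arm.

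| True events, E vs C | Assumed s_E, s_C | Recorded, E vs C | Two-sided Fisher p |
|---|---|---|---|
| 13 vs 13 | 50%, 0% | 6 vs 0 | 0.029 |
| 13 vs 13 | 40%, 0% | 5 vs 0 | 0.060 |
| 13 vs 13 | 50%, 10% | 6 vs 1 | 0.12 |
| 26 vs 13 (exercise doubles the rate) | 0%, 0% | 0 vs 0 | 1 |
| 13 vs 13 | 100%, 100% (no filter) | 13 vs 13 | 1 |

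Counts are rounded down (13 × 0.5 = 6.5; 13 × 0.4 = 5.2; 13 × 0.1 = 1.3). The p-values are:

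- 6 vs 0: 2 × C(128,6) / C(256,6) = 0.029.
- 5 vs 0: 2 × C(128,5) / C(256,5) = 0.060.
- 6 vs 1: 2 × [C(128,7) + 128 × C(128,6)] / C(256,7) = 0.12.

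The same filter can create an apparent difference or hide a real one. Whether a nominal 0.05 is crossed depends on the assumed attribution.

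**The case against.** A reader might infer that harms cannot be compared between the arms at all. The article does not support that. Deaths, non-relapse mortality, GvHD, infections, the listed symptoms and complications at discharge are all collected irrespective of attribution, and a fatal harm of exercise would enter overall survival. This part of the objection stands and sets the limits of the point.

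Three other strong readings also fail:

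- **The control rate is zero by construction.** The rule also covers events related to assessments. The article schedules the same assessments in both arms, including a maximal exercise test and strength testing, so control-arm events can be recorded.
- **There is no denominator.** It is the randomized arm; what may be biased is the numerator.
- **Causality is judged by someone who knows the arm.** The article does not say. Masking of participants and therapists is ruled out by the interventions, but an assessor could be masked, and a condensed article may leave that detail to the full protocol. A masked assessor would still depend on accounts from patients and therapists who know the arm.

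The illustration is also open to challenge: its inputs are assumed, one event fewer moves p from 0.029 to 0.060, and the Data analysis section describes no between-arm test of adverse events. The argument rests on the product formula, with the table only as illustration.

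Finally, the filter has a purpose. Transplant patients have many background events, and unrestricted recording would produce a long listing. That is a reason for a short list; it does not justify making attribution the entry condition.

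**Conclusion.** The point holds in a limited form. The safety rule is stated outright, so it is not a detail merely left to another document. As written, non-fatal events outside the separately collected categories cannot be compared between arms in the home phase without attribution bias. Falls, fractures, musculoskeletal injury, bleeding and cardiac events are the main examples.

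The size of the bias is the ratio of the two attribution probabilities. It is unknown and could go in either direction.

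The conclusion assumes that the home-phase events named here are not captured in some form the article does not mention, and that attribution is not made wholly without knowledge of the arm. It does not assume any particular event rate.

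The primary analysis of all-cause survival by intention to treat is unaffected, as is the sample size. This is a cheap improvement and not a threat to the trial's main result.

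**What to change.** Change the recording rule in the Safety issues section along these lines: *The following events are recorded in both groups from randomization to day 365, irrespective of presumed cause: falls, fractures, musculoskeletal injuries, bleeding, cardiac events (including serious adverse events of these types) and unplanned hospital readmission. Relatedness to the intervention or to an assessment is recorded separately as a descriptive item. Groups are compared as randomized on all listed events.* Events outside the list that are judged related can continue to be recorded as now.

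Ask the questions in the same words in both arms at the existing phone calls, and confirm them in the chart review already used for infections. State who assesses relatedness and whether that person is masked.

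The cost is a few extra fields on the call and chart-review forms, and more background transplant events in the listing, which the fixed list keeps within bounds. Endpoints, sample size and patient management do not change. For patients already enrolled, events that left a chart entry, such as readmissions and fractures, may be partly recoverable; falls and minor injuries probably are not, so an early change is worth more than a late one.

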### Sample size

Sample size was chosen to achieve adequate statistical power (1-β = 0.8) for detecting a difference between the exercise and relaxation group with respect to two-year overall survival (primary outcome). The calculation is based on the two-year overall survival rates of our previous RCT (0.66 in the exercise group vs 0.49 in the control group) [35]. Accordingly, 128 participants per group (total number = 256) are needed to achieve adequate power to detect a significant (two-tailed α = 0.05) difference from Kaplan-Meier estimates tested for equality by log-rank tests.

### Participants and setting

All patients, scheduled for an allo-HCT at the Heidelberg University Clinic are invited to participate in the PETRA study. Inclusion criteria are age ≥18 years and the ability to understand and follow the study protocol. Exclusion criteria comprise contra-indications for progressive exercise training, i.e. inability to walk or stand, instable bone lesions, severe neurological deficiencies, severe cardiac or cardiovascular diseases and severe pulmonary global insufficiency.

### Recruitment and randomization

All eligible patients scheduled for allo-HCT at the University Hospital in Heidelberg are briefly informed about the PETRA study during the preparation visit (about 2–3 weeks before admission for allo-HCT) by case-management. If interested, patients are then informed in detail by the PETRA study coordinator. Upon written informed consent, the patient is included in the trial and scheduled for baseline assessment (t0), which should be within 14 days prior to start of conditioning for allo-HCT.

After completion of the baseline assessments, the participant is randomly allocated to one of the two intervention groups. Allocation is done by the minimization method [68] stratified by disease, age (< 40 / ≥ 40 years of age), gender, remission state (CR/ no CR), and intensity of conditioning (full/ doses reduced). Stratification is used in the randomization process, as we anticipate these variables to have major influence on the outcome.

### Interventions

The training starts at the same day as the conditioning treatment. Both intervention programs are performed 3–5 times per week for 12 months. During the first phase (hospital stay for allo-HCT) participants perform the program 3 times under supervision and guidance of an experienced therapist, 2 times self-directed. During the second phase (after discharge), patients perform both interventions self-directed at home. Until assessment on day 100 weekly phone calls in both groups will allow for adaptation of the program and enhance motivation/ adherence, 3 training sessions per week are recommended. After day 100 assessment, phone calls will take place every 2–3 weeks.

#### Exercise intervention

All patients receive an exercise manual with background information (including contraindications for training, motivation), instructions for tailoring the training intensity (depending on clinical status), descriptions for different resistance exercises for the whole body and endurance exercises. Patients receive stretch bands and free weights for resistance exercises, for endurance exercises patients have access to a stationary bicycle (patient room) and a treadmill (hallway) during the inpatient period. We developed a self-rating instrument which helps patients to find the appropriate exercise intensity (including RPE scale) [13]. The exercise intervention complies with the ACSM exercise guidelines for cancer survivors and healthy adults and is progressed on an individual basis [6, 69]. A complete resistance training session includes 6 to 10 exercises for major upper and lower muscle groups and is recommended 2–3 times per week. Endurance training comprises bicycling or walking/jogging 3 times per week. Patients are encouraged to increase exercise intensity when they reach 3 sets of 12 repetitions for the resistance exercises or when they feel less exhausted using the RPE-scale (target 12–14 for endurance exercise, 14–16 for resistance exercise) [70]. The exercise program is performed on a very individual basis and includes also some psychological aspects e.g. motivation, goal setting, dealing with barriers, and regular feedback on physical performance data is given to promote adherence [71]. Adherence to FITT components (frequency, intensity, type, timing) will be described [72] to ensure correct interpretation of the findings. Furthermore, it is possible to perform the training in an appropriate sport/ exercise facility close to patients’ homes. Within the scope of the PETRA study we will also develop a network called ‘*OnkoActive*’, which will enable referral to specialized exercise facilities. Furthermore, within ‘*OnkoActive*’ an internet-based training platform will be developed to support the home-based intervention.

#### Relaxation intervention

The progressive muscle relaxation method according to Jacobsen does not include any aerobic or muscle strengthening components [73]. Patients receive a manual with background information, an audio CD with 2 different versions (long/ short version) and a portable CD player. Patients in the control group will receive the standard physiotherapy program and will also have access to a bicycle ergometer and treadmill during the inpatient period.

### Data analysis

The main intervention effect will be assessed on the basis of a Cox-regression analysis between exercisers and controls (relaxation group) as defined at randomization, regardless of exercise adherence, i.e. according to the intent-to-treat principle.

The differences in secondary endpoints between groups will be assessed using mixed models, which accounts for repeated observations on the same subjects over time. This method provides a more efficient estimate of the intervention effect in pretest-post-test trials than traditional methods [74]. Mixed models will also be used for testing to which extent differences between the treatment groups depend on training adherence, changes in muscle strength, cardiorespiratory fitness, and body composition. Normality assumptions will be checked and, if deviation from normality is detected the data will be transformed accordingly.

In addition, change in physical activity behavior post intervention will be monitored on an explorative basis.

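### The primary survival comparison is described without the five minimization factors; run that way it is valid and keeps its planned power, but it is conservative and less efficient than an adjusted Cox model

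*Protocol article*

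**What the plan says.** Three sections of the protocol article bear on this.

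- **Recruitment and randomization.** Allocation is by minimization, "stratified by disease, age (< 40 / ≥ 40 years of age), gender, remission state (CR/ no CR), and intensity of conditioning (full/ doses reduced"). The reason given is: "Stratification is used in the randomization process, as we anticipate these variables to have major influence on the outcome".
- **Data analysis.** "The main intervention effect will be assessed on the basis of a Cox-regression analysis between exercisers and controls (relaxation group"), with patients analysed as randomized whatever their adherence. No covariate or stratification factor is named, and none is ruled out.
- **Sample size.** The trial is sized to detect a "difference from Kaplan-Meier estimates tested for equality by log-rank tests". No strata are mentioned.

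The Background section adds that the survival effect in the group's previous RCT was adjusted for several prognostic variables, among them conditioning regime and gender.

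**The concern.** The design and the described analysis do not match. The article regards five variables as prognostic enough to steer allocation, then describes the primary comparison twice (Cox model and log-rank test) as a plain contrast of two arms.

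Balancing arms on prognostic factors reduces the real sampling variation of the treatment estimate. An arm-only model does not know about that balance, so its standard error is too large and the test rejects too rarely under the null. An arm-only Cox model also estimates a hazard ratio averaged over the factors, which lies closer to 1 than the ratio conditional on them.

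At stake is efficiency. The trial has about 109 expected deaths and a nominal power close to 80%, so information already recorded at allocation is worth using. Naming the covariates in advance also avoids having to choose them once data are in.

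**Working it through.** **Inputs from the Sample size section:** two-year survival "0.66 in the exercise group vs 0.49 in the control group"; "two-tailed α = 0.05"; "adequate statistical power (1-β = 0.8"); "128 participants per group (total number = 256) are needed".

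**Step 1. Reproduce the plan's sample size (Schoenfeld, 1:1, proportional hazards, complete two-year follow-up).**

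- HR = ln 0.66 / ln 0.49 = (−0.4155)/(−0.7133) = 0.582; ln HR = −0.540
- Events = 4 × (1.960 + 0.842)² / 0.540² = 107.5, rounded up to 108
- Mean probability of death = (0.34 + 0.51)/2 = 0.425
- Patients = 108/0.425 = 254.1, or 127.06 per arm, rounded up to 128 per arm
- At 256 patients: 256 × 0.425 = 108.8 events; power = Φ(√108.8/2 × 0.540 − 1.960) = Φ(0.86) = 80.5%

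The stated 128 per group is reproduced. It comes from marginal survival rates and an arm-only test.

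**Step 2. Compare arm-only and adjusted Cox models by simulation.** The documents give no prognostic effects, so these are assumptions:

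- five binary factors with prevalences 50%, 25%, 40%, 50% and 50%, each with the same hazard ratio;
- minimization with probability 0.8 of assignment to the favoured arm;
- exponential survival, censored at 2 years, with baseline hazard and treatment effect calibrated so that marginal two-year survival is 0.49 and 0.66;
- 256 patients, 3,000 trials per cell, Wald test at two-sided 5%. The Monte Carlo standard error is about 0.4 points for type I error and 0.7 for power.

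| Assumed HR per factor | Type I error, arm-only | Type I error, adjusted | Power, arm-only | Power, adjusted | Mean fitted HR, arm-only | Mean fitted HR, adjusted |
|---|---|---|---|---|---|---|
| 1.0 | 4.3% | 4.7% | 79.0% | 79.5% | 0.580 | 0.576 |
| 1.3 | 4.2% | 5.2% | 80.1% | 81.6% | 0.582 | 0.570 |
| 1.5 | 4.1% | 5.5% | 81.0% | 84.2% | 0.580 | 0.559 |
| 2.0 | 2.5% | 4.7% | 82.7% | 89.9% | 0.578 | 0.526 |

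Fully deterministic minimization (2,000 trials per cell) gives a similar picture. At HR 2.0, type I error is 2.6% against 5.1% and power is 82.8% against 89.4%.

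**Step 3. Read the table.**

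- Power forgone by omitting the factors: 81.6 − 80.1 = 1.5 points (HR 1.3), 84.2 − 81.0 = 3.2 (HR 1.5), 89.9 − 82.7 = 7.2 (HR 2.0).
- Arm-only power does not fall below the planned 80% at any assumed HR from 1.3 to 2.0.
- The arm-only hazard ratio stays near 0.58, the value implied by 0.66 against 0.49. The adjusted ratio moves away from 1 as the factors strengthen. The two answer slightly different questions: marginal and conditional.
- Arm-only type I errors at HR 1.3 and 1.5 (4.2%, 4.1%) cannot be told apart from the no-effect row (4.3%) given the simulation error. Only the drop to 2.5% at HR 2.0 is unmistakable.

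**Step 4. Covariates or strata.** Age group, gender, remission state and conditioning intensity have two levels each, so crossing them gives 2⁴ = 16 strata before disease is added, or 108.8/16 = 6.8 expected deaths per stratum. Full cross-stratification would be thin; covariates, with at most one or two factors as strata, are more workable.

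**The case against.** The strongest objection is that the Data analysis section is silent about covariates and does not exclude them. A journal article condenses a fuller protocol or analysis plan, and a covariate list is often left there. Sizing on an unadjusted log-rank test is common even when the analysis is adjusted, and the previous RCT's adjusted analysis suggests that this group does adjust. This stands to the extent that a reader might infer a decision to leave the factors out; the documents do not show one. The mismatch remains all the same. The article gives the model, the contrast and the analysis set, describes the comparison twice as two-group, and calls the allocation factors highly influential. Followed as written, the analysis is arm-only.

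A second objection is that nothing is broken. This also stands. A type I error below 5% is conservative and valid. The planned power is met, because the sample size was built on marginal rates and an arm-only test. The arm-only hazard ratio being nearer to 1 reflects a marginal instead of a conditional effect, and it is the marginal contrast that the assumed survival rates describe.

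Third, the size of the gain depends on assumed prognostic strengths. A hazard ratio of 2.0 for every factor, gender included, is demanding, and with weak factors the difference is within simulation noise.

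**Conclusion.** The point holds as a matter of efficiency and clear specification. The article balances allocation on five factors it considers strongly prognostic and describes a primary analysis that uses none of them. Analysed that way, the test is valid and meets its planned 80% power, but it is conservative: type I error is about 4% down to 2.5% for assumed factor hazard ratios of 1.3 to 2.0. It also gives up about 1 to 7 points of power relative to an adjusted model (80–83% against 82–90%).

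These figures rest on five equally strong binary factors, the assumed prevalences, proportional hazards and complete two-year follow-up. The article's own expectation of strong influence favours the upper part of the range, but it gives no effect sizes to confirm that.

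A reader might infer that the trial is underpowered or that its primary test is invalid. Neither follows: the stated sample size is reproduced and the error rate is not inflated.

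**What to change.** In the Data analysis section, state that the primary Cox model contains treatment arm plus the five minimization factors as covariates, or as strata where the number of events per stratum allows. Fix the grouping of disease in advance, since it may have several categories and about 108 deaths are expected. Keep the unadjusted log-rank test or arm-only Cox model as a sensitivity analysis. This preserves the link to the sample-size calculation, which need not change.

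Optional additions are age as a continuous variable in place of the cut at 40, and the baseline Karnofsky score. Table 1 of the article shows the score recorded at t0, and the Background cites a cohort study in which it independently predicted survival.

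The cost is one sentence and no new data, as all five factors must be known at allocation. The reported primary hazard ratio would be conditional on the factors and should be labelled so.
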